### Patient and public involvement

Patients and members of the public will not be involved in the design, recruitment, implementation, or reporting of this study. Study findings will be communicated to participants via email upon completion.

### Principles and methods of unblinding or breaking the blind

#### Unblinding timeline

All participants will be unblinded upon the study’s completion, specifically after the final 6-month follow-up for all subjects.

#### Unblinding method

The unblinding process will be managed by an independent Data Monitoring Committee (DMC), which will oversee the procedure and securely store all randomization data until the predetermined unblinding period.

#### Emergency unblinding

In the event of a serious adverse event (SAE) or any other emergency during the trial, immediate unblinding will be conducted to facilitate appropriate medical intervention. The principal investigator will formally request emergency unblinding from the DMC, ensuring that both the rationale and the process are thoroughly documented.

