### Safety outcomes

Safety outcomes will include the occurrence of both common and serious intraoperative or postoperative adverse events. Common adverse events consist of neck pain, dizziness, tinnitus, and mild allergic reactions, which will be evaluated by combining patient complaints with clinical observation. Serious adverse events include respiratory depression, defined as a sustained SpO_2_ of less than 90% or the need for assisted ventilation; anaphylaxis, defined as the development of anaphylactic shock; sinus bradycardia, defined as a heart rate of less than 50 beats per minute; hematoma formation; infection; severe arrhythmias; pneumothorax; and complications related to general or spinal anesthesia.

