### Randomization and blinding

An independent research staff member will generate the randomization sequence using the Sealed Envelope online tool,^1^ with a 1:1 allocation ratio, permuted blocks of 2 and 4, and stratification by age (18–64 and ≥65 years). The allocation results will be stored in sequentially numbered, sealed opaque envelopes. Patients will be randomly assigned to either the SGB group or the control group (*n* = 150 per arm). The anesthesiologists responsible for administering the intervention will be aware of group allocation due to the nature of the procedure but will not be involved in patient recruitment, data collection, or outcome assessment. Patients, surgeons, postoperative care providers, outcome assessors, and the data analyst will remain blinded to group assignments throughout the study. Successful stellate ganglion block in the intervention group will be confirmed by the occurrence of Horner’s syndrome (ptosis, miosis, enophthalmos, conjunctival hyperemia, and facial anhidrosis). Patients will not be informed whether these clinical signs occur, thereby maintaining the integrity of blinding. The schedule for patient enrollment, study interventions, and outcome assessments will adhere to the SPIRIT statement (Table 1).

**Table 1 tab1:** SPIRIT schedule of patient enrolment, study interventions and outcome assessment.

Time point	Study period									
	Enrolment	Allocation	Post-allocation					Close-out	Follow-up	
	Emergency room	15 min Pre-an	Intraoperative	Post-op	24 h Post-op	48 h Post-op	72 h post-op	Discharged	1 month	6 months
Patient enrolment										
Eligibility criteria	**×**									
Written informed consent	**×**									
Demographic data	**×**									
Baseline characteristics	**×**									
Randomization/allocation	**×**									
Study interventions										
SGB		**×**								
Sham SGB		**×**								
Outcome assessment										
CAPS-5 score									**×**	**×**
BAI score					**×**	**×**	**×**			
VAS Sleep score					**×**	**×**	**×**			
NRS Pain score					**×**	**×**	**×**			
HRV			**×**		**×**	**×**				
Recovery time				**×**						
Extubation time				**×**						
RASS score				**×**						
Length of hospital stay								**×**		
Safety Outcomes										
Neck pain			**×**		**×**	**×**	**×**			
Dizziness			**×**		**×**	**×**	**×**			
Tinnitus			**×**		**×**	**×**	**×**			
Dyspnea			**×**		**×**	**×**	**×**			
Anaphylaxis			**×**		**×**	**×**	**×**			
Sinus bradycardia			**×**		**×**	**×**	**×**			

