### Anesthesia procedures and perioperative management

All patients enrolled in this trial will undergo general anesthesia. Intraoperative monitoring will include non-invasive blood pressure (NIBP), electrocardiography (ECG), pulse oximetry (SpO_2_), and bispectral index (BIS). Anesthesia will be induced with intravenous propofol (1.5–2.5 mg/kg), combined with sufentanil (0.2–0.4 μg/kg) for analgesia. Rocuronium (0.6–0.9 mg/kg) will then be administered to facilitate muscle relaxation. Following induction, endotracheal intubation will be performed, and tube placement will be confirmed. Mechanical ventilation will be initiated to maintain end-tidal carbon dioxide between 35 and 45 mmHg.

Anesthesia maintenance will consist of continuous infusions of propofol (2–4 mg/kg/h) and remifentanil (0.1–0.2 μg/kg/min), along with 1% sevoflurane. BIS values will be maintained between 40 and 60. Intraoperative hypotension (mean arterial pressure <65 mmHg or a ≥20% decrease from baseline) and bradycardia (heart rate <50 beats/min) will be treated as needed.

All patients will receive 8 mg of ondansetron to prevent postoperative nausea and vomiting. In the postoperative ward, if the VAS pain score exceeds 4, 50 mg of intravenous flurbiprofen axetil will be administered for analgesia.

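### Emergency unblinding is ordered for any SAE, with no condition that the allocation be needed for care, while the SAE list takes in any heart rate below 50, any hematoma and any infection

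*Protocol article*

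**What the plan says.** All sections are in the protocol article.

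- **Emergency unblinding:** "In the event of a serious adverse event (SAE) or any other emergency during the trial, immediate unblinding will be conducted". The sentence goes on to give the purpose, which is to support medical care. Next comes the procedure: "The principal investigator will formally request emergency unblinding from the DMC, ensuring that both the rationale and the process are thoroughly documented".
- **Safety outcomes:** the serious events, during or after surgery, include "sinus bradycardia, defined as a heart rate of less than 50 beats per minute; hematoma formation; infection; severe arrhythmias; pneumothorax". Heart rate below 50 carries no duration, symptom or severity qualifier, and neither hematoma nor infection is graded. Respiratory depression is also on the list, defined as a sustained SpO2 "less than 90% or the need for assisted ventilation".
- **Anesthesia procedures and perioperative management:** every patient has general anesthesia and is intubated. "Mechanical ventilation will be initiated to maintain end-tidal carbon dioxide between 35 and 45 mmHg". For heart rate, "bradycardia (heart rate <50 beats/min) will be treated as needed".
- **Randomization and blinding:** patients, surgeons, postoperative care staff, outcome assessors and the data analyst "will remain blinded to group assignments throughout the study". The anesthesiologist who gives the block knows the allocation.
- **Unblinding timeline:** codes are opened after the last 6-month visit.
- **Data collection and monitoring:** SAEs go to the principal investigator at once and to the DMC within 24 h. Unblinding is not mentioned there.

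**The concern.** A code break for an individual patient is normally justified when the treating team must know the allocation to manage that patient. Here the trigger is the SAE label itself, and that label covers an event which the anesthesia section foresees at the same threshold. Staff who follow the rule would open allocations for no clinical reason. Staff who do not would breach the protocol.

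The 24 to 72 h anxiety, sleep and pain scores are patient-reported, and the primary outcome comes from a clinical interview. Blinding of patient and assessor is their main protection. The rule does not say that either is kept from the result of a code break. Safety reporting is affected too: the DMC must evaluate every SAE, including whether to change or stop the trial, and brief falls in heart rate would dilute the events that matter.

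**Working it through.** The protocol gives no rate for SAEs, for heart rate below 50 or for code breaks, so there is no figure of the plan to reproduce. The check compares sections and then adds an illustration of size.

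**1. Is need a condition?** The unblinding sentence is worded as an action that will follow an SAE. Its purpose clause explains why, and the investigator's request explains how. Neither says that the code stays closed when the allocation would not alter care.

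**2. What triggers it?** Safety outcomes places any heart rate below 50 among the serious events. The anesthesia section uses the same threshold for an intraoperative event that is treated as needed. Exclusion criteria remove bradyarrhythmia with a baseline rate below 50, so such a reading would generally be a new, countable event.

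**3. When would the breaks occur?** Table 1 records safety events intraoperatively and at 24, 48 and 72 h. It places anxiety, sleep and pain scores at 24, 48 and 72 h, and CAPS-5 at 1 and 6 months. A break for an intraoperative event precedes all of these. A break for any event recorded by 72 h precedes the 1-month CAPS-5.

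**4. Who learns the allocation?** Emergency unblinding does not say. Postoperative care staff, who would meet an event at 24 to 72 h, are among those who are to stay blinded.

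**5. How many patients?** Expected number = 150 × control rate + 150 × SGB rate, with 150 per arm from Sample size calculation. All rates below, the proportion of patients with at least one heart rate below 50, are assumptions.

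| Control / SGB rate | Control + SGB patients | Total of 300 | Share |
|---|---|---|---|
| 2% / 2% | 3 + 3 | 6 | 2% |
| 5% / 5% | 7.5 + 7.5 | 15 | 5% |
| 5% / 10% | 7.5 + 15 | 22.5 | 7.5% |
| 10% / 10% | 15 + 15 | 30 | 10% |
| 10% / 20% | 15 + 30 | 45 | 15% |
| 20% / 30% | 30 + 45 | 75 | 25% |

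The total runs from 6 to 75 patients. The arms differ only in rows where a difference was put in.

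**The case against.** The strongest reply is that the section should be read as a whole. It names a medical purpose and requires a formal request with a documented rationale, which suggests case-by-case judgment. Data collection and monitoring sends SAEs to the DMC without mentioning unblinding. Emergency unblinding is an ordinary exception to blinding, and an event that is treated as needed can also be recorded as an SAE. This softens the point but does not remove it: the text never says that the code may stay closed after an SAE, and it does not limit who is told.

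A reader might also infer four stronger things, which the document does not support.

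- **That all 300 patients would be unblinded**, because everyone is ventilated. The words "or the need for assisted ventilation" belong to a definition of respiratory depression, and planned ventilation after intubation is not that. The wording needs tidying, but this is no forecast.
- **That many patients would be unblinded.** No event rate is given, and at 2% per arm the number is 6.
- **That one arm would be unblinded more than the other.** A sympathetic block could plausibly change how often the heart rate falls below 50, but no rate by arm is given. For hematoma, the needle technique is stated to be the same in both groups. The literal ventilation reading would affect both arms equally.
- **That the primary outcome would be biased.** CAPS-5 assessors are to be blinded, and the anesthesiologist giving the block already knows the allocation. A break during surgery might therefore reveal nothing new to that person and never reach patient or assessor. The principal investigator's supervision of data entry does not by itself create outcome bias.

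**Conclusion.** The concern holds as a conflict between stated rules. Emergency unblinding, taken with Safety outcomes, requires code breaks for events where the allocation need not be known. Randomization and blinding and Unblinding timeline require the blind to be kept to the end. This is more than missing detail, because the rule is stated and would do avoidable damage if followed.

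Its size cannot be determined from the document. The range of 6 to 75 patients rests wholly on assumed rates and covers heart rate below 50 alone; hematoma and infection are not counted. Bias in the 1-month PTSD comparison is possible and depends on who is told. The point should be corrected, but it does not by itself invalidate the design.

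**What to change.** 1. Reword Emergency unblinding so that the code is broken only when knowing the allocation is needed to manage the patient. Disclose it only to those treating the patient. State that the CAPS-5 assessor and the analyst, and the patient where possible, stay blinded. Documentation of rationale and process is already required; add who was told and when.
2. Reconcile Safety outcomes with the anesthesia, data monitoring and unblinding sections. Define an SAE by the seriousness of its consequence. Record other instances of heart rate below 50, hematoma and infection as adverse events of interest, so that they are still counted and compared by arm.
3. State that planned ventilation under general anesthesia does not meet the respiratory depression item. Keep intraoperative sustained SpO2 below 90% as an event. Confining the item to the time before induction and after extubation would lose it.

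The cost is a short amendment, case report form guidance and re-labelling of events already logged as SAEs. Breaks already made cannot be undone, but they can be listed by arm and kept from the assessors for the interviews still to come. How any of these events is treated does not change.

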## Discussion

The randomized, double-blind, placebo-controlled trial, involving 300 adults at two centers, was designed to evaluate SGB for the prevention of PTSD after emergency ocular trauma. The primary objective is to evaluate the effect of SGB prevention in patients with ocular trauma by the incidence of PTSD 1 month after surgery. Secondary objectives include the severity of PTSD, delayed-onset PTSD, four symptom clusters, the severity of dissociative symptoms, as well as BAI score, VAS sleep score, NRS pain score, HRV, recovery time, extubation time, and RASS score. This study will be conducted in accordance with the Consolidated Standards of Reporting Trials (CONSORT) guidelines (24). To enhance the credibility of the primary outcome, baseline variables were adjusted, and sensitivity analyses were conducted to evaluate the stability of the findings. These methodological strategies were implemented to ensure the accuracy, consistency, and reliability of the results.

The stellate ganglion, also known as the cervicothoracic sympathetic ganglion, is part of the cervical sympathetic chain and is formed by the fusion of the inferior cervical and first thoracic ganglia in approximately 80% of individuals (25, 26). Its anatomical location is relatively constant, typically situated anterior to the C7 transverse process and superior to the neck of the first rib (25, 26). Stellate ganglion block (SGB) exerts its therapeutic effect by injecting local anesthetics near the stellate ganglion to inhibit peripheral sympathetic nerve activity. Several studies have demonstrated the effectiveness and safety of SGB in alleviating PTSD-related symptoms (14–18). In a cohort of 166 military personnel reported by [name] et al., approximately 70% of those who received SGB at the C6 level experienced a significant reduction in PTSD Checklist (PCL) scores, with benefits persisting for 3 to 6 months post-procedure (27). Furthermore, a multicenter randomized clinical trial involving military patients with PTSD found that repeated SGB procedures, administered biweekly, led to improvements in symptoms such as depression, anxiety, pain, physical function, and overall psychological well-being (23).

In this study, we will perform a right stellate ganglion block under ultrasound guidance. Ultrasound-guided SGB is a safe and effective method (19). The right side was chosen on the basis of functional hemispheric lateralization, as previous studies have demonstrated right-sided dominance of the sympathetic nervous system and neural circuits related to fear and anxiety (23, 28, 29). Unilateral blockade is sufficient to modulate sympathetic activity while minimizing the risk of complications associated with bilateral procedures, such as recurrent laryngeal nerve palsy or phrenic nerve paralysis.

This randomized controlled trial investigates the potential of SGB to prevent PTSD in patients undergoing emergency ocular trauma surgery. Mechanistically, PTSD is characterized by chronic overactivation of the sympathetic nervous system, which promotes excessive consolidation of fear memories, manifesting clinically as recurrent flashbacks and hypervigilance (30, 31). This hyperadrenergic state is thought to be driven by elevated levels of nerve growth factor (NGF), which facilitates sympathetic sprouting and increases systemic norepinephrine (NE). SGB may counteract this process by downregulating NGF and/or NE, thereby disrupting the pathological sympathetic feedback loop and mitigating the development of PTSD-related symptoms (32). Our previous preclinical study further supports this hypothesis, demonstrating that SGB attenuated conditioned fear memory formation in mice by inhibiting noradrenergic projections from the locus coeruleus to the basolateral amygdala (20).

Visual deprivation resulting from ocular trauma may enhance emotional sensitivity and facilitate the encoding of fear-related memories, possibly through heightened activation of the amygdala, a key brain region involved in emotional processing and memory consolidation (33, 34). SGB may exert its preventive effect on PTSD by inhibiting sympathetic outflow at the stellate ganglion level, thereby attenuating excessive amygdala activation and potentially disrupting the early consolidation of fear memories following trauma (20, 31).

This study has several limitations. First, the follow-up duration is limited to 6 months, which may not be sufficient to determine the long-term sustainability of SGB’s preventive effect on PTSD. Future studies could evaluate long-term efficacy by extending follow-up to 12 months or beyond. Second, the intervention involves a single SGB procedure. Although feasible in emergency settings, this design precludes evaluation of cumulative or repeated-block protocols that may produce more robust or durable outcomes. The dose–response relationship thus remains unclear. Third, while heart rate variability (HRV) is included as an objective physiological measure, other mechanistic markers such as plasma catecholamine levels or functional neuroimaging (for example, amygdala activity on fMRI) are not assessed. Finally, the study population is restricted to adults with ocular trauma treated at two centers in China, which may limit the generalizability of the findings to other trauma types, healthcare systems, or cultural contexts.

The primary purpose of this study is to evaluate whether SGB, administered during the acute perioperative period of ocular trauma surgery, can prevent the onset of PTSD. Unlike previous research that has mainly focused on SGB as a treatment for chronic PTSD, our trial targets its potential as a preventive intervention during the critical early window of fear memory consolidation. Patients with ocular trauma represent a uniquely high-risk group, as sudden vision threat, appearance changes, and functional loss markedly increase vulnerability to PTSD. Current strategies for prevention rely largely on psychosocial support delivered after discharge, and effective biological interventions are lacking. By targeting sympathetic hyperactivity, SGB may disrupt pathological memory formation and offer a rapid, low-cost, and feasible approach that can be seamlessly integrated into routine trauma surgery workflows. If successful, this study could not only establish SGB as a preventive strategy in high-risk trauma populations but also provide a new framework for incorporating early biological interventions into acute surgical care.
